### Control arm

After randomization, subjects allocated to the control group will receive one 30-min individual session, provided by a coordinator, about the importance of healthy eating and physical activity to prevent type 2 diabetes [4, 22]. The toolkit, including leaflets about healthy eating and instructions for physical activity, is presented to participants in control group. They are instructed to visit a public healthcare center for follow-up, and no additional education is provided.

### Intensive lifestyle intervention (LSI) core program

The LSI protocol was developed based on the U.S. DPP and a previous literature review related to community-based intervention studies [4, 22]. The major goals of the C-KDPS LSI program are: 1) a minimum of 5–7% loss of initial body weight in 6 months and to maintain this weight loss throughout the study period, 2) increased physical activity of at least 150 min/week with moderate-intensity activity, 3) balanced healthy eating habit, and 4) cessation of smoking and alcohol with stress management. The intensive LSI program is a systematically organized system using web-based program, designed to motivate, empower, and encourage the participants for long-term adherence [23]. Trained C-KDPS coordinators (background in nursing) deliver all the intervention sessions using a web-based system.

The LSI program curriculum is delivered in 18 sessions over 24 weeks (Table 2). During the first 12 weeks, all participants are instructed to visit every week. After one session of orientation, instructions for modifying lifestyle, dietary intake, physical activity, and self-monitoring are introduced for all 18 sessions. During latter 12 weeks, the program focuses on adherence to the LSM. After the 24-week period, personal contact and monitoring are scheduled for at least every 2 months at the public healthcare centers to check adherence to the LSM. The coordinators have the primary responsibility for delivering the LSM program, conducting maintenance sessions, motivating the participants to keep their LSM, assessing the attainment of the goal, and acquisition of required data. All the coordinators are registered nurses, and C-KDPS manuals are provided to minimize the differences among the educators and standardize the intervention contents.

**Table 2 Tab2:** Comparison of core curriculum between DPP and C-KDPS

Session	DPP	C-KDPS
1	Welcome to the lifestyle balance program	Welcome to the C-KDPS program
2	Be a fat detective	How to exercise?
3	Three ways to eat less fat	Reason to lose body weight
4	Healthy eating	Right walking
5	Move those muscles	Healthy eating 1
6	Being activity	Aerobic exercise
7	Tip the calorie balance	Healthy easting 2
8	Take charge of what’s around you	Stretching exercise
9	Problem solving	Food exchange
10.	The four keys to healthy eating out	Aerobic exercise
11	Talk back to negative thoughts	Food exchange
12	The slippery slope of lifestyle change	Whole body Resistance exercise
13	Jump start your activity plan	Elastic band exercise
14	Make social cues work for you	Eat out healthy
15	You can manage stress	Lower body strengthening exercise
16	Ways to stay motivated	Eating for hypertension, hyperlipidemia
17		Core exercise
18		Giving up drinking and no smoking

### Web-based program construction and its use

The web site was designed to coordinate the C-KDPS process. It is composed of four parts: 1) personal information; 2) LSM program implementation (instruction, goal setting, education materials, case-report form, and recommendations); 3) mutual communication among participants, health coordinators, and committees (counseling, Q&A, free contact to coordinators); and 4) planner function (things to do, visit schedule) (Fig. 2).

**Fig. 2 Fig2:**
[figure not shown]
Study outline of this C-KDPS. Two healthcare centers in Chungju city and Suwon City were selected. The study was controlled and monitored by the Catholic Medical center in Seoul, Korea. A lifestyle intervention (LSI) program was performed through an internet-based web program that included education contents, goal setting and prescription, monitoring, counseling, and a scheduler. The principal investigator, the steering committee, and the coordinators (educators) communicated with each other in real time via the web site

As body weight change is a main parameter of each visit, the target goals for the next visit (body weight, exercise time, and dietary calorie) are automatically calculated, based on current body weight. The 7% weight loss goal is presented, and participants are encouraged to achieve this target. If the participants achieve the target body weight, maintenance of the weight is encouraged. If the participants lose more than 7% of initial body weight, they are recommended to maintain the weight that they have lost, as long as their BMI exceeds 21 kg/m^2^ [4]. During the core program, the participants visit the healthcare centers for 24 weeks, and join in supervised physical activity at every visit. The coordinators teach the exercise skills using video on the web site. The video file is available during the study period at any convenient time and place for participants. Supporting materials, such as pedometer (Mi Band, Xiaomi Inc., China), toolkit, exercise band, and hand grips are given after a supervised and corresponding class. The participants are instructed in the use of the equipment at the healthcare center and then take the equipment home. The fat and calorie goals are used to achieve the weight loss goal, not as goals for healthy eating. Dietary modification is set to achieve total daily calorie intake, and the calorie goals are calculated automatically, based on current body weight [4, 9].

Participants are instructed to use a “keeping track booklet” to record their food intake and adherence to physical activity every week for 24 weeks. At every visit, the subjects bring their booklets and review the contents with coordinator. The coordinator reinforces and encourages the subjects’ diet and exercise habits, while also measuring adherence to the LSI. If the participant fails to visit the public healthcare center, the coordinator tries to make contact by cell phone or text message. Subjects’ self-reported exercise and dietary habits are collected, as are data that they enter on the web site. Frequency and duration of physical activity are estimated on a weekly basis using questionnaires. Dietary intake is measured using a simple food frequency questionnaire. This process takes about 40–60 min every visit. The coordinators provide the LSM prescriptions and discuss participants with detailed plans.

### Maintenance strategy

After completion of the core curriculum for 24 weeks, the participants are instructed to visit every month for the next 6 months, and every 2 months thereafter, until the end of the study (Table 3). If they cannot visit the centers, the coordinator contacts them by phone and via the web site. As retention of participants throughout the study period is very important, a healthy lifestyle camp, group teaching, or a reinforcement program is scheduled for at least two classes per year to deliver messages about healthy eating, maintenance of weight goal, behavioral topics, and motivational programs.

**Table 3 Tab3:** Frequency of management for each group while undertaking the prevention program

Intensive lifestyle intervention group			Control group	
subject prescription, education, monitoring		Management frequency	subject education	Management frequency
			(Only prescription)	
1-12 weeks	1/ week	12	1-12 weeks	1
13-24 weeks	1/2 weeks	6	13-24 weeks	1
25-48 weeks	1/month	6	25-48 weeks	1
1-2 years	2/month	5	1-2 years	1

### Training of coordinator and investigators

All coordinators are obliged to attend a biannual 1-day training session. At the initiation meeting, coordinators are instructed in the C-KDPS protocol, all intervention manuals, interview skills, and how to use the web site. After 6 months, the training program is scheduled to review LSI data, discuss the education process, role playing, maintenance skills, and feedback of the feasibility about the web-based program. The steering committee holds regular meetings with investigators and staff from two centers at least 2 times per month to review and check the study process.

### Study outcomes

The primary outcome is new development of diabetes diagnosed by 2016 ADA criteria. A 75-g OGTT with HbA1c level testing is scheduled at 6, 12, 18, and 22 months. Secondary outcomes consist of cardiovascular disease (CVD) risk factors, changes in demographic characteristics with pancreatic β-cell function, insulin sensitivity, lifestyle habits, quality of life, feasibility or compliance of bidirectional web-based program, and health costs for the C-KDPS.

### Statistical analysis

The C-KDPS sample size was determined for the primary outcome (between-group difference in diabetes incidence) at 22 months’ follow-up with type 1 error(α) = 0.05 and power (1-β) ≥ 0.80. We aimed to detect a cumulative incidence difference of 11% between the two intervention groups (control group = 19.8% vs. intensive LSI group = 8.6%) based on previous studies [7, 9]. A total of 420 subjects should be recruited, considering the dropout rate of 25% during the study period.

The primary and secondary outcomes will be analyzed using the intention-to-treat approach. Differences in participants’ baseline characteristics and clinical outcomes between two groups were evaluated by a two-sample *t*-test for continuous outcomes and by a Chi-square test or Fisher’s exact test for categorical outcomes. A mixed-model analysis of covariance, including treatment group, gender, age, and the terms and baseline values of clinical parameters, will be used to assess the effects of intervention in a post-intervention survey. For the primary outcome—the comparison of cumulative incidence of diabetes between two groups—a log-rank test with random effects for intercept to account for pre-post correlations within individuals will be used. An interaction effect between time and intervention group will be assessed first. If there is no interaction effect, the overall intervention difference will be assessed. Otherwise, the intervention difference will be assessed at each time point. Adherence to the LSI program is measured by evaluating class attendance, weight loss goal at 6 months, maintenance of physical activity, and achievement of diet goal. For long-term effects of intervention, cost-effectiveness analysis will be analyzed using the Markov model [24].

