### Randomization

In this study, a stratified blocked randomization strategy will be used to achieve between-group comparability, and to avoid imbalance in the number of subjects in each stratum. The randomization entails measuring the level of the stratified factors—center and sex—for eligible subjects, determining to which stratum each belongs, and using a block size of 4 within each stratum. Stratified blocked randomization in both centers will be conducted by study staff not involved in the intervention through a central computerized process. The sequence of group allocations will be concealed until after the baseline data collection is completed.

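### For continuous secondary outcomes the plan names both unadjusted two-sample tests and a baseline-adjusted mixed model without saying which decides, and the model's listed covariates omit centre, a stratification factor

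*Protocol article*

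**What the plan says.** All of this is in the protocol article under Methods.

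- **Unadjusted tests.** Statistical analysis says that differences in "baseline characteristics and clinical outcomes between two groups were evaluated by a two-sample" t-test for continuous outcomes, and by Chi-square or Fisher's exact test for categorical ones. Baseline characteristics and clinical outcomes are named as two separate things.
- **Adjusted model.** The next sentence gives "A mixed-model analysis of covariance, including treatment group, gender, age, and the terms and baseline values of clinical parameters" and assigns this model to estimating the intervention effect after baseline. One entry in the covariate list is garbled and may mean visit terms. Centre is not named.
- **Primary outcome.** New diabetes has its own test, a log-rank test, named in a separate sentence.
- **Randomisation.** The Randomization section says "a stratified blocked randomization strategy will be used to achieve between-group comparability", and the procedure involves "measuring the level of the stratified factors—center and sex—for eligible subjects", with blocks of 4 in each stratum.

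**The concern.** Read together, the two sentences give a continuous secondary outcome, such as a cardiovascular risk factor or insulin sensitivity, two between-group analyses. One ignores the baseline value, the repeated visits and both stratification factors. The other uses baseline and sex but not centre. The two can disagree, and the article does not state which is the result.

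Two things are at stake. The first is precision, because a comparison that ignores a correlated baseline is less efficient. The second is freedom to choose: if either analysis may be reported, the chance of a false positive rises above the nominal level. The missing centre term is a smaller matter. Stratifying the allocation and then leaving the factor out of the analysis makes standard errors too large when that factor is prognostic.

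This is more than detail left to a statistical analysis plan, because the article itself names both tests and gives an explicit covariate list.

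**Working it through.** **1. The plan's own figure.** Inputs from Statistical analysis: "type 1 error(α) = 0.05 and power (1-β) ≥ 0.80"; "control group = 19.8% vs. intensive LSI group = 8.6"%; "We aimed to detect a cumulative incidence difference of 11% between the two intervention groups"; "A total of 420 subjects should be recruited, considering the dropout rate of 25% during the study period". A two-sided test and 1:1 allocation are assumed.

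Per-arm size, pooled two-proportion formula: n = [1.96·√(2·p̄·(1−p̄)) + 0.8416·√(p1(1−p1) + p2(1−p2))]² / (p1−p2)².

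- With the stated 11-point difference (19.8% vs 8.8%): [1.96·0.4951 + 0.8416·0.4889]² / 0.11² = 1.909 / 0.0121, so n = 158. Then 158/0.75 gives 211 per arm, 422 in total.
- With the exact rates (19.8% vs 8.6%): n = 152, 203 after dropout, 406 in total.
- At 420 × 0.75 = 315 completers (157.5 per arm), power for the exact rates is 0.816.

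So 420 is reproduced closely. It concerns the primary outcome and does not depend on this point.

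**2. Unadjusted t-test against baseline adjustment.** The article gives no standard deviation or baseline-to-follow-up correlation ρ, so ρ is an assumption. With equal variance σ² at both times, the variances (up to the common factor 2/n) are:

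- baseline-adjusted analysis: σ²(1−ρ²);
- t-test on follow-up values: σ², so the sample-size factor is F = 1/(1−ρ²);
- t-test on change scores: 2σ²(1−ρ), so F = 2(1−ρ)/(1−ρ²) = 2/(1+ρ).

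The standard-error ratio is √F. For an effect that the adjusted analysis detects with 80% power, t-test power is about Φ((1.96+0.8416)/√F − 1.96).

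| ρ (assumed) | Follow-up: F | SE ratio | Power | Change: F | SE ratio | Power |
|---|---|---|---|---|---|---|
| 0.5 | 1.33 | 1.15 | 68% | 1.33 | 1.15 | 68% |
| 0.7 | 1.96 | 1.40 | 52% | 1.18 | 1.08 | 73% |
| 0.9 | 5.26 | 2.29 | 23% | 1.05 | 1.03 | 78% |

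The article does not say which kind of value the t-test would use.

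**3. Omitting centre.** This was simulated: 316 analysed, four centre-by-sex strata with blocks of 4, one follow-up value, ρ = 0.6, a sex effect of 0.3 SD, a treatment effect of 0.25 SD or none, and 4,000 replicates. All effect sizes are assumptions. The centre effect is the part that baseline does not explain. Both adjusted analyses include sex.

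| Centre effect (SD) | 0 | 0.3 | 0.6 | 1.0 |
|---|---|---|---|---|
| Power: t-test on follow-up value | 60% | 58% | 57% | 51% |
| Power: adjusted, without centre | 79% | 78% | 74% | 67% |
| Power: adjusted, with centre | 79% | 79% | 78% | 79% |
| Type I error: t-test | 4.3% | 4.9% | 4.3% | 2.5% |
| Type I error: adjusted, without centre | 4.9% | 4.5% | 4.0% | 2.1% |
| Type I error: adjusted, with centre | 5.0% | 4.8% | 5.2% | 5.4% |
| Type I error: either t-test or centre-free model significant | 7.4% | 7.1% | 6.5% | 3.7% |

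The Monte Carlo error on a 5% rate is about √(0.05·0.95/4000) = 0.3 percentage points.

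**The case against.** The best defence is that the article already implies an order. Only the mixed model is assigned to estimating the intervention effect. The two-sample sentence has no such purpose, pairs outcomes with baseline characteristics, never mentions follow-up and is in the past tense, while the model and log-rank sentences look forward. Simple description first, then a model, is a coherent reading. This carries weight: the model is probably the intended analysis. But the order is implied, and clinical outcomes still stand in the sentence on unadjusted tests.

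Several stronger readings are tempting, and the document does not support them:

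- *The weaker test could supply the primary result.* It could not under the plan as written, because diabetes incidence has its own named test.
- *Every outcome is tested twice.* The mixed-model analysis of covariance is a method for continuous outcomes. No second test is shown for categorical secondary outcomes, so there is no contradiction there.
- *The t-test would be repeated at each of the four visits.* The article does not say so.
- *The loss is up to fivefold.* That needs a t-test on raw follow-up values and a correlation of 0.9. The Study outcomes section describes some secondary outcomes as changes, and for change scores the same correlation gives 1.05.
- *Leaving out centre biases the results.* It does not. Type I error falls below 5%, and a material power loss (67% vs 79%) needs a 1 SD centre difference, for which the article gives no evidence.

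It can also be said that a one-sentence model description in an article is not a full covariate list. That is fair, but naming one of two stratification factors and not the other reads as an oversight.

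**Conclusion.** The point holds in a limited form, for secondary outcomes. The article names two analyses for continuous clinical outcomes without stating which is decisive, and the adjusted one lists sex but not centre.

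The size depends on assumptions that the article cannot settle. For correlations of 0.5 to 0.9, relying on the t-test is equivalent to needing 1.33 to 5.3 times the participants on follow-up values, or 1.33 to 1.05 times on change scores. If either analysis could be reported at will, the false-positive rate would be about 7% when the centre effect is small. That describes the room the wording leaves, not a stated intention. Omitting centre costs about one percentage point of power at a 0.3 SD centre effect and about 12 points at 1 SD. The harm is lost precision and an unclear order of analyses. This is a modest defect that is worth correcting because the correction is nearly free.

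**What to change.** In Statistical analysis, and in the statistical analysis plan to match:

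1. Restrict the two-sample t, Chi-square and Fisher tests to descriptive comparison.
2. Name the baseline-adjusted mixed model as the single between-group analysis of continuous secondary outcomes.
3. Add centre to its covariates, and replace the garbled entry with an explicit statement of the visit terms if that is what is meant.
4. Optionally, analyse binary secondary outcomes stratified by centre and sex, for example with a Cochran-Mantel-Haenszel test or a logistic model. This is an improvement, not the repair of a contradiction.

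The cost is wording and one degree of freedom for the two centres. The model is already planned and centre is known for every participant. No new data are needed.

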## Methods

### C-KDPS steering committee

The community-based KDPS (C-KDPS), is an intensive LSI program that was developed by the C-KDPS steering committee from the two Diabetes Centers of the Catholic University of Korea (Seoul St. Mary’s Hospital and St. Vincent’s Hospital) and the Institute of U-Healthcare core in December 2015. The committee members are composed of the principal investigator from each clinical center, a diabetologist, a diabetes educator, a registered dietitian, exercise physiologists, and a web programmer. The C-KDPS program was based on the U.S. Diabetes Prevention Program (DPP). After an extensive literature review, the committee members developed the C-KDPS study protocol on the basis of recommendations from the SPIRIT statement on randomized trials (Table 1) [19]. The principal investigator of each center plays a role in the communications between the committee and two public healthcare centers in Chungju City and Suwon City in Korea. The committee members held regular meetings to check the process of preparing, tracking, and updating the progress on implementing the C-KDPS program in the two cities every week from December 2015. The lifestyle modification (LSM) protocol and development process was reviewed and approved by IRBs of St. Vincent’s hospital (No. VC16MISI0003) and Seoul St. Mary’s hospital (No. KC16EISI0234). This trial has been registered with the Clinical Research Information Service (CRIS), Republic of Korea (KCT0001981). This C-KDPS program protocol has also been reviewed and certified by the Korean Diabetes Association.

**Table 1 Tab1:** Proposed timeline of C-KDPS

Year	2016		2017				2018				2019
Term	3	4	1	2	3	4	1	2	3	4	1
Enrollment											
1^st^ screening	X	X									
2^nd^ screening		X	X								
Informed consent		X	X								
Allocation		X	X								
Intervention											
LSI		X	X	X	X	X	X	X	X	X	
Assessment											
6-month FU				X	X						
12-month FU						X	X				
18-month FU								X	X		
22-month FU										X	X
Web system											X

*FU* follow-up

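### Centre is a stratification factor that no stated analysis uses, and the primary log-rank test is described without centre or sex; adding them is free and recovers a small amount of precision if they are prognostic

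*Protocol article*

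**What the plan says.** The Randomization section of the protocol article describes stratified blocked allocation, "measuring the level of the stratified factors—center and sex—for eligible subjects", and "using a block size of 4 within each stratum". The section on the steering committee places the trial in "two public healthcare centers in Chungju City and Suwon City in Korea", so there are two centres by two sexes, or four strata.

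The Statistical analysis section sets out three kinds of comparison:

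- **Simple between-group tests** (t-test, Chi-square, Fisher's exact), with no adjustment mentioned.
- **A mixed model** for the clinical parameters: "A mixed-model analysis of covariance, including treatment group, gender, age, and the terms and baseline values of clinical parameters". Sex is listed, and so is age, which was not a stratification factor. Centre is not listed.
- **A log-rank test** for the primary outcome, cumulative incidence of diabetes. A random intercept is mentioned; centre and sex are not.

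No analysis in the article uses centre. The article gives no figure for how strongly centre or sex predicts diabetes or any secondary outcome.

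**The concern.** Stratified blocks force the arms to be nearly balanced within each centre-by-sex group. If those groups differ in risk, the balance makes the treatment comparison more precise than simple randomisation would. An analysis that ignores the strata estimates its variance as though the balance had not been imposed. The standard error is then too large, the test slightly conservative and the confidence interval slightly wide. The trial pays for the balance in its design and does not collect the benefit in its analysis.

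A centre effect is plausible here. The two centres are in different cities, and coordinators at the healthcare centres deliver the sessions. The article itself says that manuals are issued to limit differences between educators. What is at stake is efficiency and agreement between design and analysis, not the validity of the result.

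**Working it through.** **Inputs from the article.** Two centres and two sexes; blocks of 4; "with type 1 error(α) = 0.05 and power (1-β) ≥ 0.80"; "control group = 19.8% vs. intensive LSI group = 8.6"% at 22 months; "A total of 420 subjects should be recruited, considering the dropout rate of 25% during the study period"; glucose testing at 6, 12, 18 and 22 months.

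**Assumptions, because the article is silent.** 1:1 allocation, two-sided alpha, near-equal strata, exponential dropout, and the prognostic strength of each factor, varied from a hazard ratio (HR) of 1 to 4. An ordinary log-rank test is used, because a log-rank test with a random intercept is not a standard procedure.

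**Step 1: reproduce the sample size.**

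- HR = ln(1 − 0.086) / ln(1 − 0.198) = 0.408.
- Freedman's formula: [(1 + 0.408)/(1 − 0.408)]² × (1.96 + 0.842)² gives 45 events after rounding up.
- Mean incidence (0.198 + 0.086)/2 = 0.142; 45/0.142 = 317; 317/0.75 = 423.
- Two-proportion formula with the rounded 11-point difference (19.8% versus 8.8%): 158 per arm; 316/0.75 = 422.

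Both results agree with the stated 420.

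**Step 2: the log-rank test with and without strata.** 4,000 simulated trials per row, 420 randomised in blocks of 4 within four strata, 25% dropout, events detected at the scheduled visits, overall incidences held at 19.8% and 8.6% (19.8% in both arms for type I error).

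| HR of the two factors | Power, unstratified | Power, stratified | Gain (points) | Type I error, unstratified |
|---|---|---|---|---|
| 1 and 1 | 86.2% | 86.1% | about 0 | 4.7% |
| 1.5 and 1.5 | 87.5% | 87.7% | 0.2 | 4.2% |
| 2 and 1.5 | 87.4% | 87.8% | 0.4 | 4.9% |
| 2 and 2 | 87.0% | 87.6% | 0.6 | 4.5% |
| 3 and 2 | 88.2% | 89.5% | 1.3 | 4.3% |
| 4 and 4 | 87.6% | 90.1% | 2.5 | 3.3% |

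The Monte Carlo standard error is about 0.5 points for each power and 0.35 points for type I error. The stratified test's type I error ranged from 4.0% to 5.3%.

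A second simulation at HR 0.408 set the spread of control incidence across strata directly. Unstratified versus stratified power was 86.8% versus 86.8% for a 14–26% spread, 86.9% versus 87.5% for 8–33%, and 85.7% versus 87.5% for 5–40%.

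**Step 3: continuous outcomes.** Suppose centre explains a share R² of residual variance and is left out.

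- Ratio of reported to true standard error = 1/√(1 − R²). At an assumed R² = 0.05 this is 1/√0.95 = 1.026, or 2.6% too large.
- True size = 2 × [1 − Φ(1.96 × 1.026)] = 4.4%.
- A test with 80% power when centre is included has Φ(2.802 − 1.96 × 1.026) = Φ(0.791), about 78.5%, when it is not.
- For scale, with equal-sized centres d²/4 = R²/(1 − R²), so R² = 0.05 means a gap of about 0.46 SD between the two centres.

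**The case against.** The strongest reply has four parts.

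1. **The loss is conditional.** It exists only if centre or sex is prognostic, and the article gives no evidence on that. This stands. A reader might infer from the omission that power is certainly lost; the documents do not support that.
2. **The loss is small.** The larger gains need large differences between strata, among people who all have prediabetes and a BMI of at least 23 kg/m². For continuous outcomes, adjustment for baseline values, a central laboratory and standardised manuals should absorb part of any centre difference. This also stands.
3. **There is no threat to validity or to planned power.** A reader might infer that false positives rise or that the trial is underpowered. Neither follows. The unstratified test errs on the conservative side, and its power stayed above 0.80 in every setting at the design effect. Simulating a weaker effect, such as HR 0.5, does give powers of about 67–70%, but nearly all of that shortfall comes from the weaker effect and not from omitting the strata.
4. **The article condenses a fuller plan.** It does not say that the log-rank test is unstratified, and such detail is often left to an analysis plan. This has some force for the log-rank test taken alone. It has less for the mixed model, where the article lists covariates, keeps one stratification factor and omits the other. The list does contain an unexplained reference to terms, which may mean visit or time, but nothing shows that it means centre.

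The point also should not be widened to say that both factors are ignored everywhere: sex is in the mixed model.

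**Conclusion.** The mismatch is real and modest. Randomisation is stratified by centre and sex, the listed mixed-model covariates include only sex, and the primary test as described uses neither.

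To the extent that the factors are prognostic, the stated analyses are slightly conservative. At the design effect the log-rank test loses about 0 to 0.6 power points for moderate factors (HR 1.5 to 2 each) and about 1 to 2.5 points for strong ones. The differences at the lower end are of the same order as the simulation error. For continuous outcomes, standard errors would be about 2.6% too large if centre explained 5% of residual variance.

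These sizes rest on assumed prognostic strength, equal strata, 1:1 allocation, a two-sided test and exponential dropout. The direction of the effect does not depend on those particular values. The case for acting is that the improvement is nearly free, not that the trial is at risk.

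**What to change.** In the Statistical analysis section, state that the primary log-rank test is stratified by centre and sex (four strata). Add centre as a fixed effect to the mixed model that already includes sex, and say what the unexplained terms in that model are.

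The cost is a few words. Both variables are recorded before allocation, so no data collection changes, and the sample size of 420 need not change. If the factors turn out not to be prognostic, stratifying costs essentially nothing (86.1% versus 86.2% power in the simulation). Settling this before outcome data are examined also rules out a later choice between adjusted and unadjusted results.

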After initial screening, the participants are instructed to visit their nearby public healthcare centers after overnight fasting. With the informed consent process, the subjects perform a 75-g oral glucose tolerance test (OGTT), HbA1c level, and questionnaires regarding lifestyle habits. Additional blood sampling is done at 30 and 120 min for PG, insulin, and C-peptide levels using the standardized manual of operations [21], and shipped to the central laboratory within 24 h of sample collection. The questionnaires contain self-reported personal data about medical history, employment, education, economic status, smoking or alcohol use, and lifestyle habits including diet and physical activity habits. If the glucose and HbA1c levels of subjects are within the pre-diabetic range, the subjects are recommended to participate in this C-KDPS. In addition, demographic data and a standard 12-lead electrocardiogram are obtained. Anthropometric and laboratory analysis are scheduled to be conducted at baseline, 6, 12, 18, and 22 months.

Recruitment of participants began on July 1, 2016. The enrollment of the participants is expected to be complete by the end of January 2017. Intervention and follow-up of study subjects will be ongoing until December 2018.

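### The primary log-rank comparison uses neither baseline glycaemia nor the randomisation strata, a modest loss of efficiency that pre-specified adjustment would recover

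*Protocol article*

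**What the plan says.** The Statistical analysis section names the primary method: "For the primary outcome—the comparison of cumulative incidence of diabetes between two groups—a log-rank test". The sentence goes on to add a random intercept for within-person correlation, but lists no covariate and no strata. The sentence before it lists group, gender, age and baseline values, but for a mixed-model analysis of covariance of clinical parameters, and does not extend that list to diabetes incidence.

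The relevant baseline data already exist. Under Recruitment, at the second screening step and after an overnight fast, "the subjects perform a 75-g oral glucose tolerance test (OGTT), HbA1c level, and questionnaires regarding lifestyle habits". Entry is on fasting glucose, 2-hour glucose or HbA1c in the pre-diabetic range. Under Study outcomes, the endpoint is new diabetes by ADA criteria, tested by OGTT and HbA1c at 6, 12, 18 and 22 months.

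The Randomization section stratifies by centre and sex, "using a block size of 4 within each stratum". Baseline glycaemia is not a stratification factor.

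**The concern.** Diabetes is declared when one of these glycaemic measures crosses a threshold. How far a participant starts from the threshold should therefore predict the outcome. The primary test leaves that information out, and it also leaves out the two factors used to stratify randomisation.

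Two things are at stake. The first is power, in a trial that expects only about 45 to 50 events. The second is chance imbalance. Glycaemia is balanced only on average, so an uneven split would carry into the unadjusted hazard ratio, and any adjustment chosen after seeing it would be post hoc.

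**Working it through.** **Inputs from the Statistical analysis section.** "type 1 error(α) = 0.05 and power (1-β) ≥ 0.80" (two-sided assumed); "control group = 19.8% vs. intensive LSI group = 8.6" per cent at 22 months; 25% dropout; "A total of 420 subjects should be recruited". Allocation is taken as 1:1. The hazard ratio per SD of baseline glycaemia is not in the article, so a range is assumed.

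**Reproducing 420.**
- Hazard ratio under proportional hazards: ln(1 − 0.086) / ln(1 − 0.198) = 0.408.
- Freedman events: (1.960 + 0.842)² × (1.408 / 0.592)² ≈ 44.3, so 45.
- Mean incidence: (19.8 + 8.6) / 2 = 14.2%. Subjects: 45 / 0.142 = 317. After dropout: 317 / 0.75 = 423, against 420 stated.
- Completers: 420 × 0.75 = 315. The two-proportion formula then gives 81.6% power.

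The plan therefore meets its own target without adjustment.

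**Effect of adjustment at the planned effect.** Event times were simulated under proportional hazards and read at the four visits, with the marginal incidences held at 19.8% and 8.6%. There were 4,000 runs per row. Each cell gives power without and then with one baseline glycaemia score as covariate.

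| Assumed HR per SD | 316 complete subjects | 420 randomised, 25% dropout | Relative efficiency |
|---|---|---|---|
| 1.35 | 80.7% → 81.1% | 85.5% → 86.2% | 1.01 |
| 1.65 | 80.3% → 81.7% | 85.7% → 86.1% | 1.02–1.03 |
| 2.0 | 81.6% → 84.2% | 85.2% → 87.9% | 1.06 |
| 2.7 | 80.2% → 85.5% | 85.7% → 90.0% | 1.13 |

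The right-hand design has more power because those who drop out late still contribute events (about 50, against 45). The simulation standard error of one power figure is about √(0.857 × 0.143 / 4000) = 0.6 points. In sample-size terms, 1 − 1/1.06 is about 6% fewer subjects and 1 − 1/1.13 about 12%. Type I error at HR 2.0 was 4.2% unadjusted and 3.7% adjusted, so there was no inflation.

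A separate simulation with a complementary log-log grouped-time model (2,500 runs, 420 randomised, 25% dropout) gave 86% → 87%, 86% → 89% and 87% → 91% at HR 1.5, 2.0 and 2.5.

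**Smaller treatment effect.** The planned reduction is 1 − 8.6/19.8 = 57%. The Background cites 42% for diet plus exercise in the Da-Qing study. At 42%, the grouped-time simulation gave 58% → 59%, 58% → 62% and 57% → 65% at HR 1.5, 2.0 and 2.5, each figure with a simulation error of about 1 point.

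**Chance imbalance.** With 210 per arm, the standard error of the between-arm difference in a standardised score is √(2/210) = 0.098 SD. An imbalance of two standard errors is 0.195 SD. At HR 2.0 per SD it shifts the unadjusted hazard ratio by a factor of about exp(0.693 × 0.195) = 1.14, in either direction.

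**Change of estimand.** With marginal incidences fixed, the true treatment hazard ratio given the covariate is 0.392 at HR 2.0 per SD and 0.373 at 2.7, against 0.408 with no covariate effect. The adjusted figure is conditional and is not interchangeable with the unadjusted one.

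**The case against.** The strongest reply is that nothing here is an error. The unadjusted log-rank test is valid under randomisation, the trial was sized for it, and the power target is met. All of that stands. A reader might infer that the primary result would be biased or the trial underpowered as planned; the article's own figures support neither.

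The size of the gain also rests on an assumed prognostic strength. A further repeat of the grouped-time simulation found no gain at HR 1.5 (87.0% and 86.9%), and 86.8% → 90.1% at 2.0. That stands too: if prognosis is weak, the power gain is negligible.

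It is tempting to argue that the either-or entry rule makes baseline levels vary widely. The article does not support this. Candidates are first screened on fasting glucose of 100–125 mg/dL, and the pre-diabetic limits cap all three measures. No baseline spread is reported, and the simulations used an untruncated normal score with a correctly specified linear effect, which favours adjustment.

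Covariates are often left to an analysis plan, and this is a condensed article. But the article does name the primary test, and it lists covariates for the other model. Its random-intercept clause needs rewriting in any case, since a log-rank test has no intercept; that is a separate and larger fault in the same sentence.

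**Conclusion.** The point holds as a modest, nearly free gain in efficiency, and not as an error in the plan. At the planned effect it is worth about 0 to 1.5 points of power at an assumed HR per SD of 1.35 to 1.65, about 3 at 2.0, and about 4 to 5 at 2.5 to 2.7. At a 42% reduction it is about 1 to 8 points over HR 1.5 to 2.5. Pre-specified adjustment also removes the effect of a chance imbalance in baseline glycaemia from the estimate. These figures assume 1:1 allocation, two-sided testing, proportional hazards, and one correctly specified score in place of several separate covariates.

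**What to change.** Replace the primary-analysis sentence so that the estimate and test are the treatment term of a grouped-time (complementary log-log) proportional-hazards model over the four visits, stratified by centre and sex. Fix a small set of continuous baseline covariates in advance: fasting glucose, 2-hour glucose and HbA1c, with age if events allow. Treatment plus four covariates is five coefficients, or about 9 to 10 events each at 45 to 50 events, so the list should not grow. Full stratification gives 2 centres × 2 sexes × 4 visits = 16 baseline terms; if that is judged too many, enter centre and sex as main effects, and settle this before unblinded data are seen.

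Delete the random-intercept wording in the same edit. Report the unadjusted log-rank test stratified by centre and sex, and the cumulative incidences by arm, as supportive. State that the adjusted hazard ratio is conditional on the covariates.

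The cost is wording only: no added subjects, visits or tests. The one drawback is the conditional hazard ratio, which the unadjusted incidences offset.
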